## 12. SAFETY RATING

### 12.1. ADVERSE EVENTS

All adverse events (AEs) will be recorded in the data collection notebooks from the moment the patient signs his or her informed consent. As a general rule, the term of diagnosis of the disease will be used. If it is not available, or if the researcher does not consider it Symptoms or clinical signs can be collected as adverse events until a definitive diagnosis is available.

A deterioration in laboratory or complementary test values, vital signs, or other safety variables, compared to baseline baseline data, should only be reported as an adverse event:

- If it meets any of the criteria to be considered a serious adverse event, or
- If it is the reason for discontinuation of treatment with the investigational product.

For each adverse event recorded in the data collection notebook, the investigator will assess the severity (see section 12.2), the causal relationship (see section 12.3) of these events

with the cell therapy or treatment received (unrelated, unlikely, possible, probable, safe) and/or with any trial procedure and severity (see section 12.3).

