##### Safety:

- Incidence of AE, SAE, AR, as well as SUAR, throughout the intervention period in patients in the experimental group, as well as in the 12 months after the end of treatment, compared to the control group.

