#### Visit 5. Treatment Visit (Week 4 - Day +21)

1. Date of the visit.
2. Vital signs (blood pressure, heart rate).
3. Correct palpation of tibial and pedal pulses.
4. Evaluation of the ulcer:
  - A) Macroscopic observation of the injury: epithelialization tissue, presence of exudate and existence of bleeding, using the Resvech scale.
  - B) Wound extension by means of a graduated ruler, measuring the greatest vertical length (length) and the longest perpendicular length (width). Photographs will be taken with the ruler located on the injury to evaluate the evolution of the wound and the measurement of the perimeter.
5. Sample collection for the exudate study (annex 3).
6. Evaluation of quality of life using the CIVIQ 20 questionnaire.
7. VU treatment (Annex 2/Annex 4).
8. It will be recorded in the medical record if there has been any concomitant change in your medication since the last visit.
9. It will be recorded in the clinical history if any adverse event or death has occurred since the last visit.

Follow-up visits (up to 12 months after the last treatment)

Subsequently, once the patient has completed the 4-week treatment period, 9 efficacy and safety follow-up visits (visits 6 - 14) will be made at 42, 49, 56, 63, 70, 77 and 84 days from the start of treatment.

In the event that patients living in nursing homes have been included in the trial, the follow-up visits, once the 4-week period of treatment has ended, may be carried out if the principal investigator considers it necessary, in the residence itself, as has been done during the usual follow-up of these patients.

This additional follow-up will focus on evaluating the progression of the injury after treatment and the long-term safety of ADSCs.

The follow-up visit to the evolution of the injury will be structured as follows:

1. Date of the visit.
2. Vital signs (blood pressure, heart rate).
3. Blood test (hemoglobin, leukocytes, lymphocytes, neutrophils, and platelets), biochemistry (creatinine, bilirubin, GOT, GPT, GGT, albumin, triglycerides, and total cholesterol) and coagulation (PT, PTT, and fibrinogen) (Visit 14).
4. Correct palpation of tibial and pedis pulses.
5. Evaluation of the ulcer:
  - A) Macroscopic observation of the injury: epithelialization tissue, presence of exudate and existence of bleeding, using the Resvech scale.

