### 8.4. TRIAL INTERRUPTION

The study will be interrupted if any of the following circumstances are met:

1. Serious toxicity (grade 3-4 NCI CTC-AE) related to investigational drug in 3 patients.
2. Serious infections (grade 3-4 NCI CTC-AE) related to the administration procedure in 3 patients.
3. Investigational drug-related mortality in 1 patient

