## 12.2. DEFINITIONS

An adverse event (AE) is defined as any adverse medical episode or experience in a patient or clinical trial subject receiving the experimental treatment (including the comparator group), even if it does not necessarily have a causal relationship to that treatment. This may include any unfavorable or unintentional signs or symptoms, an abnormal laboratory finding (including blood tests, x-rays, or scans), a temporary illness associated with the use of study cell therapy, or a worsening of a pre-existing condition. A disorder

Persistent is a clinical condition (including a disorder being treated) that was diagnosed before the subject signed informed consent and is documented in the subject's medical history. In addition, any event associated with an overdose of the product will also be considered an adverse event.

Medical or surgical procedures (e.g., endoscopy or appendectomy) are not considered an adverse event; The adverse event is the medical condition that gives rise to the procedure.

A procedure-related adverse event is an AE that appears during a study

It is not related to the investigational product, but which, in the opinion of the investigator, is related to some procedure of the trial. For example, a harmful episode that

It is related to a medical procedure required by the protocol such as the surgical conditioning of the patient necessary to administer the investigational drug. The AEs considered as related to the procedure will be analyzed in isolation, although they will be considered a part of the total related AAs of the study.

Adverse Reaction (AR) An AR is any harmful, unintended reaction to an investigational drug, regardless of the dose administered. Unlike an AE, there is a causal relationship to the investigational drug (possible, probable, or certain relationship).

A Serious Adverse Event (SAE) is defined as any unwanted experience that affects a patient, whether or not it is considered related to the treatment of the protocol and that results in:

- Death.
- A life-threatening event (i.e., there was a risk of immediate death of the patient at the time the reaction was observed).
- Hospitalization or prolongation of a hospitalization.
- Persistent or significant disability/incapacity.

- A congenital anomaly or a birth defect in descendants.

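### The AE reporting rule in 12.1 is narrower than the definition in 12.2 and depends on stopping a product that controls never receive; 1.11 also compares AR and SUAR with an arm where both are zero by definition

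*Protocol*

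**What the plan says.** Section 12.1 limits when a worsening in laboratory or complementary tests, vital signs or other safety variables becomes an adverse event. Such a change, "compared to baseline baseline data, should only be reported as an adverse event", must satisfy one of two conditions: "If it meets any of the criteria to be considered a serious adverse event, or" the second, "If it is the reason for discontinuation of treatment with the investigational product".

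Section 12.2 defines an AE for both arms, comparator included, and gives as one example "an abnormal laboratory finding (including blood tests, x-rays, or scans"). It attaches no condition of seriousness or discontinuation. Sections 12.2 and 12.5.1 then require all AEs to be recorded.

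In section 7, blood is drawn at visit 1. The follow-up list ends its blood-test item with "and coagulation (PT, PTT, and fibrinogen) (Visit 14"). No other post-baseline panel is named in the visit text.

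Safety is a main variable. Section 1.11 defines it as the incidence of AE, SAE, AR and SUAR over the intervention period "as well as in the 12 months after the end of treatment, compared to the control group". Section 10.1 lists the same four categories without the comparison. On AR, section 12.2 says: "Unlike an AE, there is a causal relationship to the investigational drug (possible, probable, or certain relationship"). It defines SUAR as a serious AR that does not fit the baseline safety information.

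**The concern.** Three features of the wording affect what the main safety variable counts.

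- A non-serious laboratory finding can be an AE to a site that follows 12.2 and not reportable to a site that follows 12.1. Nothing in the protocol says which governs.
- The discontinuation condition presupposes a product that can still be stopped. That is not so at the scheduled post-dose panel in either arm, and it is never so in controls.
- Two of the four categories compared with control in 1.11 are defined by causality to a drug that controls do not receive.

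At stake is a safety count that depends on which section a site reads, that is ascertained differently by arm during the dosing weeks of an open-label 10 versus 10 trial, and that includes comparisons which carry no information about the control arm.

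**Working it through.** The protocol gives no figure to reproduce here. The check is one of timing and definitions, with arithmetic only to show scale.

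**Timing.** The last dose is at visit 5, day 21. Visits 6 to 14 run to day 84. Section 7 lists seven days for these nine visits, but the last is day 84, so that is visit 14. The lag from last dose to the panel is 84 − 21 = 63 days.

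**Can each 12.1 condition be met?**

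| Situation | Serious | Reason for stopping the product |
|---|---|---|
| Experimental arm, dosing weeks (vital signs, unscheduled tests) | possible | possible |
| Control arm, dosing weeks (same measurements) | possible | impossible: no product (9.6) |
| Either arm, visit 14 panel | possible | impossible: dosing ended 63 days earlier |

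At visit 14 only the seriousness condition remains, equally in both arms. The arms differ during dosing, when vital signs are taken at every treatment visit and unscheduled tests may occur.

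**Scale at visit 14.** Let p be the assumed proportion of patients with a non-serious laboratory deterioration found there. Expected number uncounted among 20 is 20p; the chance of at least one is 1 − (1 − p)^20.

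| p (assumed) | 20p | Chance of at least one |
|---|---|---|
| 5% | 1 | 64% |
| 10% | 2 | 88% |
| 20% | 4 | 99% |
| 30% | 6 | >99% |

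Under 12.1 none of these is an AE.

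**Scale of the asymmetry during dosing.** Suppose each arm has the same assumed proportion p of patients whose treatment ends because of a non-serious change. The experimental arm then reports 10p AEs on average: 1, 2 or 3 for p = 10%, 20% or 30%. The control arm reports 0 at every p.

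**AR and SUAR.** An AR needs a possible, probable or certain link to the investigational drug, and a SUAR is a subset of AR. Controls get the same care without the sheet (9.6), so both are 0/10 by definition. Section 11 prescribes chi-square or Fisher tests between groups for qualitative variables. Two-sided Fisher p-values against a fixed 0/10:

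- 4/10 versus 0/10: p = 0.087
- 5/10 versus 0/10: p = 0.033

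These depend only on the experimental count and are the same however well or badly controls tolerate their care.

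**The case against.** The best defence is that 12.2 gives a broad definition and 12.1 an operational rule for when a test value alone is reported. Section 12.2 says only that an AE may include a laboratory finding, and narrower reporting conventions are common. This softens the conflict but does not remove it, because the protocol also requires all AEs to be recorded and does not reconcile the two.

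It also stands that little is lost from the database. Visit 14 values are recorded and can be described under section 11. Section 12.1 still collects a diagnosis, or symptoms and signs, behind an abnormal value. The seriousness criteria admit medically important conditions, and section 8.2 has the date and reason of a withdrawal for abnormal laboratory values entered in the notebook in either arm. What is missing is the count as AEs, not the data.

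On AR and SUAR, 10.1 omits the control comparison, and 12.1 assesses causality against the cell therapy or the treatment received. The first makes the two sections inconsistent. The second does not change the AR definition in 12.2, which names the investigational drug.

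A reader might infer three stronger things that the documents do not support:

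- **That such events are kept out of the stopping count.** Section 8.4 counts "Serious toxicity (grade 3-4 NCI CTC-AE) related to investigational drug in 3 patients". If serious is meant literally, the event already passes the first condition of 12.1. If it means severe, 8.4 still does not require the toxicity to be a reportable AE first.
- **That visit 14 laboratory AEs are recorded unevenly by arm.** At that visit the second condition fails in both arms.
- **That the 31% upper 95% bound for 0/10 measures what this rule loses.** That bound holds for any ten-patient arm with no events.

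**Conclusion.** The point holds within these limits and should be fixed; it does not undermine the design. Section 12.1 is narrower than 12.2 and conflicts with the duty to record all AEs. Its second condition cannot be met at the one post-baseline panel named in the visit text and never in controls. Non-serious laboratory deteriorations found at visit 14 therefore fall outside the AE count in both arms. During dosing, a non-serious change that ends treatment is an AE in the experimental arm only. The comparison of AR and SUAR with control in 1.11 is uninformative by definition. The AE and SAE definitions themselves do cover both arms.

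The size rests on assumed rates: about 1 to 4 of 20 patients uncounted at visit 14 for rates of 5% to 20%, and 1 to 3 of 10 against 0 of 10 for the dosing-period asymmetry at rates of 10% to 30%. The timing rests on the visit text, because the upper rows of Annex 1 are illegible, and on patients who kept to the dosing schedule.

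**What to change.** - Reconcile 12.1 with 12.2 through a single reporting rule for laboratory, vital-sign and other safety deteriorations that does not depend on stopping the investigational product. If the sponsor wants a threshold, it is the sponsor's choice, but it should be stated and applied identically in both arms.
- Align 1.11 and 10.1, and limit the between-arm safety comparison to all-cause AEs and SAEs.
- Report AR and SUAR descriptively for the experimental arm.

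The cost is wording in 12.1, 12.2, 1.11 and 10.1, with no new samples or visits. The downside is a few more recorded AEs. The change is best made before events are classified, since recoding later in an open-label trial would be done with the arm known.

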## 12.2. DEFINITIONS

An adverse event (AE) is defined as any adverse medical episode or experience in a patient or clinical trial subject receiving the experimental treatment (including the comparator group), even if it does not necessarily have a causal relationship to that treatment. This may include any unfavorable or unintentional signs or symptoms, an abnormal laboratory finding (including blood tests, x-rays, or scans), a temporary illness associated with the use of study cell therapy, or a worsening of a pre-existing condition. A disorder

Persistent is a clinical condition (including a disorder being treated) that was diagnosed before the subject signed informed consent and is documented in the subject's medical history. In addition, any event associated with an overdose of the product will also be considered an adverse event.

Medical or surgical procedures (e.g., endoscopy or appendectomy) are not considered an adverse event; The adverse event is the medical condition that gives rise to the procedure.

A procedure-related adverse event is an AE that appears during a study

It is not related to the investigational product, but which, in the opinion of the investigator, is related to some procedure of the trial. For example, a harmful episode that

It is related to a medical procedure required by the protocol such as the surgical conditioning of the patient necessary to administer the investigational drug. The AEs considered as related to the procedure will be analyzed in isolation, although they will be considered a part of the total related AAs of the study.

Adverse Reaction (AR) An AR is any harmful, unintended reaction to an investigational drug, regardless of the dose administered. Unlike an AE, there is a causal relationship to the investigational drug (possible, probable, or certain relationship).

A Serious Adverse Event (SAE) is defined as any unwanted experience that affects a patient, whether or not it is considered related to the treatment of the protocol and that results in:

- Death.
- A life-threatening event (i.e., there was a risk of immediate death of the patient at the time the reaction was observed).
- Hospitalization or prolongation of a hospitalization.
- Persistent or significant disability/incapacity.

- A congenital anomaly or a birth defect in descendants.
- Any other major medical conditions (i.e., major adverse events that are not immediately life-threatening and do not result in death or hospitalization but may be life-threatening or may require intervention to prevent another of the outcomes listed above, e.g., cancer) according to appropriate medical criteria.
- Suspected transmission of an infectious agent through a drug.

Serious and unexpected adverse reaction (SUAR): A serious adverse reaction whose nature, severity or outcome is not consistent with the baseline safety information.

Toxic death is defined as death secondary to toxicity. This must be specified on the death report form: the cause of death must be listed as [toxicity]. The assessment of toxic deaths is independent of the assessment of response (patients may die from toxicity after a complete assessment of response to treatment).

Hospitalization is defined as the official admission to a hospital for a period of more than 24 hours. Hospitalization and prolongation of hospitalization are criteria for the severity of an AE; however, they are not considered by themselves a SAE. If there is no AA, the investigator should not report hospitalization or prolongation of hospitalization as a SAE. This is the case in the following situations:

- Hospitalization or prolongation of a hospitalization is needed to perform a procedure required by the protocol.
- Hospitalization or prolongation of a hospitalization is part of a routine procedure of the center (e.g., removal of a vascular stent after surgery).
- Hospitalization due to a pre-existing condition that has not worsened.

All AEs and SAEs suffered by subjects from the signing of the informed consent until the end of their participation in the study should be recorded.

The investigator or his or her collaborator will question and/or examine the patient for signs of adverse events. Questioning of patients regarding the possible occurrence of adverse events should be done in a general way (e.g., "How it has been felt since the last visit?"). The patient should not be questioned about the presence or absence of specific adverse events.

Promoter: Andalusian Network of Design and Translation in Advanced Therapies - Andalusian Public Foundation Progress and Health M. P.

SERIOUS ADVERSE EVENTS MUST BE REPORTED IMMEDIATELY, WITHIN 24 HOURS AFTER THEIR OCCURRENCE TO THE SPONSOR ACCORDING TO THE PROCEDURE DETAILED IN THIS PROTOCOL.

12.3. ASSESSMENT OF THE CAUSALITY AND SEVERITY OF AAS

The investigator will make the causality assessment using the following definitions:

| Relationship | Definition                                                                                                                                                                                                                                                                                                               |
|--------------|--------------------------------------------------------------------------------------------------------------------------------------------------------------------------------------------------------------------------------------------------------------------------------------------------------------------------|
| UNRELATED    | There is no evidence of any causal relationship.                                                                                                                                                                                                                                                                         |
| IMPROBABLE   | There is little evidence to suggest a causal relationship (e.g., the event did not occur within a reasonable period of time after administration of study cell therapy). There is another reasonable explanation for the event (e.g. the patient's clinical condition, other concomitant treatments).                    |
| POSSIBLE     | There is evidence to suggest a possible causal relationship (e.g., because the event occurred within a reasonable time after administration of the study cell therapy). However, the influence of other factors may have contributed to the event (e.g. the patient's clinical condition, other concomitant treatments). |
| LIKELY       | There is evidence to suggest a causal relationship and the influence of other factors is unlikely.                                                                                                                                                                                                                       |
| SURE         | There is clear evidence to suggest a causal relationship and a possible contribution of other factors can be ruled out.                                                                                                                                                                                                  |

For causation assessments, events that meet the categories of safe, probable or possibly will be considered "related". Events that are improbably related or unrelated will be considered unrelated. If the investigator believes that a SAE is likely to be unrelated (unlikely related) or unrelated to the study drug, he or she must provide an alternative cause for the study.

The intensity or severity of AEs should be classified according to the common terminological criteria for Events Adverse (CTCAE) Version in effect (

[https://ctep.cancer.gov/protocolDevelopment/electronic\\_applications/ctc.htm](https://ctep.cancer.gov/protocolDevelopment/electronic_applications/ctc.htm) ). If they are not described, the following definitions may be used to qualify the severity of each AE:

|         |                                                                                                                                                                                                            |
|---------|------------------------------------------------------------------------------------------------------------------------------------------------------------------------------------------------------------|
| Grade 1 | Slight; asymptomatic or mild symptoms, only clinical or diagnostic observations, no intervention indicated.                                                                                                |
| Grade 2 | Moderate; minimal, local or non-invasive intervention; limitation of the instrumental activity of daily life.                                                                                              |
| Grade 3 | Severe; severe or of medical significance but not an immediate threat to the life; hospitalization or prolongation of hospitalization indicated; incapacitating; Limitation in self-care of daily activity |
| Grade 4 | Life-threatening; Urgent intervention required                                                                                                                                                             |
| Grade 5 | Death                                                                                                                                                                                                      |

A distinction must be made between the severity and severity of AEs. An AE that is evaluated as Grade 4 (life-threatening) should not be confused with an SAE. Severity is a category used to rate the intensity of an event; and both an AE and an SAE can be assessed as Grade 4. An event is defined as "serious" when it meets one of the criteria described above in Section 16.2

